## Abstract

**ABSTRACT:**

**Introduction:**

Secondary spontaneous pneumothorax (SSP) is a medical emergency where the lung collapses in the presence of underlying chronic lung disease. Current international clinical guidelines advise intercostal drain (ICD) insertion for SSP. However, in a previous small study needle aspiration (NA) has been shown to reduce length of hospital stay (LOHS) and reduce complications. We are evaluating the clinical and cost-effectiveness of an initial NA approach to the management of patients with SSP in the United Kingdom.

**Methods and analysis:**

The PRINCE-SSP (Pragmatic non-inferiority Randomised trial Investigating Needle aspiration vs ChEst drain for Secondary Spontaneous Pneumothorax) trial is a pragmatic, multicentre, open-label, parallel, two-group, randomised, non-inferiority trial to establish whether NA for SSP is non-inferior in terms of LOHS compared with ICD. We aim to recruit 110 patients from at least 15 UK NHS hospitals, over 18 months. Participants allocated to the intervention (NA) group will have an NA inserted at the presentation. Those allocated to the comparator (usual care) group will have an ICD inserted. Participants are followed up for 30 days. The primary outcome measure is initial LOHS, up to day 30 postrandomisation. Secondary outcomes include (but are not limited to) total LOHS including readmissions, complications, cost-effectiveness and patient-reported quality of life.

**Ethics and dissemination:**

This trial received Health Research Authority (HRA) approval from Wales Research Ethics Committee seven ethics committee (23/WA/0085). Results will be submitted for publication in a peer-reviewed journal. A plain English summary of the trial results will be prepared and disseminated with the help of our patient advisory group, including via social media, and provided to trial participants via post or email according to their preference.

**Trial registration number:**

ISRCTN12644940.

STRENGTHS AND LIMITATIONS OF THIS STUDYThe trial uses techniques already used in other types of pneumothoraces, with anticipated rapid translation of results into routine clinical management of secondary spontaneous pneumothorax (SSP), and incorporation into national and international guidelines.Patients with absent or diminished capacity can be recruited, to expand generalisability to critically unwell patients who are unable to consent at presentation.The trial involves an economic evaluation to determine the cost-effectiveness of needle aspiration versus intercostal drain of SSP.Blinding to treatment allocation is not possible for clinicians or participants.

## Introduction

 Secondary spontaneous pneumothorax (SSP) is a medical emergency where the lung collapses in the presence of underlying chronic lung disease, such as chronic obstructive pulmonary disease (COPD). It is the most common cause of spontaneous pneumothorax, with 6000 patients per year admitted to hospitals with SSP in England.^1^ SSP causes significant breathlessness and pain and results in higher morbidity, mortality and longer hospital admissions than patients with pneumothoraces and no underlying lung disease (‘primary spontaneous pneumothorax’ (PSP)).^2^ SSP typically occurs in the elderly and people with comorbidities, with an average age of 60–65.^3^

Current management of SSP is the insertion of an intercostal drain (ICD) to drain the pneumothorax.^4 5^ The drain requires a chest wall incision, guidewire insertion and dilation of the entry tract. It is then stitched into place and attached to a drainage system (underwater seal drain) for at least 24 hours and requires hospital admission for all patients, with an average length of stay of 10 days.^6 7^ An alternative method is needle aspiration (NA), where a small-bore cannula is inserted into the chest and the air is manually aspirated with a syringe, before removing the cannula as soon as all the air is removed. This takes approximately 20 min and is a one-off procedure. NA is a simpler procedure than a chest drain, less painful for patients, less time-consuming for clinicians, associated with fewer complications and can lead to same-day discharge.^8^

The use of NA in PSPs has been extensively studied, with 11 reported randomised controlled trials comparing NA to ICD.^9^,^20^ These studies have shown NA to be an effective method for managing PSP, with a meta-analysis demonstrating a significant mean reduction in length of hospital stay (LOHS) of 2.55 days (95% CI: 2.24 to 2.87) in favour of NA.^4^ Based on these studies, the European Respiratory Society 2024 advises NA as a first-line option in patients with PSP,^5^ and all UK emergency, acute and respiratory physicians are trained in NA and perform it regularly.^6^

While the less invasive, immediate drainage technique offered by NA appears also desirable for patients with underlying lung disease (ie, patients with SSP), concerns about the efficacy of NA in SSP were raised from two small case series reports.^21 22^ This has been challenged by the findings of a recent randomised study,^17^ which recruited 48 patients with SSP as part of a larger cohort of patients, which also included 79 patients with PSP.^17^ In the SSP subgroup, median (IQR) LOHS in the NA arm was 2.5 days (1.2–7.8) versus 5.5 days (3.6–9.2) in the chest drain arm (p=0.049). NA was also associated with higher rates of immediate success in the SSP subgroup: 59% for NA compared with 23% in the chest drain group (p=0.011). Importantly, complication rates across all patients were much higher in the chest drain arm than NA (15 serious complications vs none).^17^

### Aims and objectives

The Pragmatic non-inferiority Randomised trial Investigating Needle aspiration versus ChEst drain for Secondary Spontaneous Pneumothorax (PRINCE-SSP) trial will test whether NA is no worse than ICD in patients with SSP with respect to initial LOHS while demonstrating benefits in other important patient-reported, clinical and cost-effectiveness outcomes.

Specific objectives are:

To test whether NA is non-inferior to chest drain with respect to initial LOHS during 30 days from randomisationIf NA is non-inferior to usual care, to assess whether NA is superior to chest drain with respect to initial LOHSTo estimate between-group differences in patient-reported outcomesTo estimate between-group differences in clinical outcomesTo estimate between-group differences in healthcare resource usage and costsTo assess the cost-effectiveness of NA versus ICD

## Methods and analysis

### Trial design

The PRINCE-SSP trial is a pragmatic, multicentre, open-label, parallel, two-group, randomised, non-inferiority trial.

### Setting

Participants will be recruited from 20 hospital sites across England and Wales (see table 1). Each site must have an emergency department (ED) or acute medical unit (AMU). All sites will treat and manage continued care for trial participants as per usual NHS care.

**Table 1 T1:** Recruiting **h**ospitals

Addenbrooke’s Hospital, Cambridge	Royal London Hospital, London
Blackpool Victoria Hospital, Blackpool	Royal United Hospital, Bath
Canterbury Hospital, East Kent	Sheffield Teaching Hospitals NHS Foundation Trust Sheffield
Glenfield Hospital, Leicester	Southmead Hospital, Bristol
Hull Royal Infirmary, Hull	St James’s Hospital, Leeds
Macclesfield Hospital, East Cheshire	Torbay and South Devon NHS Foundation Trust. Torbay
Musgrove Park, Taunton	University College London Hospitals NHS Foundation Trust, London
Norfolk and Norwich University Hospitals Trust, Norfolk	University Hospital of Wales, Cardiff
Oxford University Hospital NHS Foundation Trust, Oxford	University Hospitals Plymouth NHS Trust, Plymouth
Princess Alexandra Hospital, Harlow	Wythenshawe Hospital, Manchester

### Trial population

The target population is patients with a diagnosis of SSP, presenting to emergency, acute medical and respiratory departments at a UK hospital. Patients may be eligible if they are at least 18 years of age, and the treating clinician believes that the pneumothorax is of sufficient size and symptoms for the treating physician to consider intervention with ICD. SSP is defined in this trial as defined as a pneumothorax occurring in a patient with known underlying lung disease, or in a patient at least 50 years of age with significant smoking history or in a patient with suspected underlying lung disease with radiology confirming structural lung disease. Exclusion criteria are bilateral pneumothorax, traumatic or iatrogenic pneumothorax, clinical concerns of tension pneumothorax, younger than <18 years of age or known pregnancy (figure 1).

**Figure 1 F1:**
[figure not shown]
Trial schema illustrating the pathway for PRINCE-SSP (Pragmatic non-inferiority Randomised trial Investigating Needle aspiration versus ChEst drain for Secondary Spontaneous Pneumothorax) participants. ICD, intercostal drain.

### Primary outcome

Initial LOHS from randomisation, up to 30 days after randomisation. This will be calculated to the nearest hour. To enable supporting analyses of the primary outcome, every attempt will be made to collect the date of discharge if beyond day 30, to calculate the initial LOHS for all participants.

### Secondary outcomes

The secondary outcomes will capture the possible advantages of the intervention for patients in terms of reduced pain, complications and improved health-related quality of life in the short term, as well as inform a formal cost-effectiveness analysis.

Secondary outcomes are as follows: (1) total number of days in hospital up to 30 days after randomisation, including readmissions; (2) immediate treatment success: for NA, success defined by persistent adequate response following the aspirations; for ICD, success is defined by adequate response with removal of drain within 72 hours of drain insertion; (3) hospital readmission within the first 30 days after randomisation; (4) pain (assessed using Numerical Rating Scale) and breathlessness (MRC Dyspnoea Scale^23^), measured postintervention (within 24 hours), daily over first 5 days and at day 30 postrandomisation; (5) patient-reported health status (EuroQol 5 dimension 5 level [EQ-5D-5L] and short form 36 [SF-36] questionnaire) measured postintervention (within 24 hours), day 5 and day 30 postrandomisation; (6) Clinical Frailty Scale^24^ measured postintervention and day 30 postrandomisation; (7) X-ray resolution (taken during routine care visit) at day 30 postrandomisation; (8) complications (yes/no for relevant predefined events) up to day 30 postrandomisation; (9) total number of subsequent pleural procedures (a) within first 24 hours and (b) up to day 30 postrandomisation; (10) mortality within the first 30 days after randomisation; (11) hospital resource use up to day 30 postrandomisation, including emergency, admitted, critical and outpatient care; (12a) cost-effectiveness: the incremental cost per each of the following secondary outcomes: pain, breathlessness and number of complications prevented when NA is compared with chest drain over 30 days; (12b) cost-utility: the incremental cost per quality adjusted life year (QALY) (gained) when NA is compared with ICD over 30 days.

### Sample size

Three relevant randomised studies have compared NA and ICD over the last decade at the time of protocol drafting^17^,^19^; two included patients with only PSP, and one included patients with both PSP and SSP. Synthesis of LOHS in these studies yields a mean between-group difference of −2.5 days (95% CI: −3.5 to −1.6) in favour of NA and pooled SD of 3.8 days. The median LOHS in the SSP subgroup (n=48) was 2.5 days in the NA arm versus 5.5 days in the chest drain arm, with a pooled SD of 4.7.^17^

The study aims to recruit 110 participants and, allowing for up to 5% mortality rate within 30 days and nominal loss to follow-up/incomplete routine LOHS data, expects to collect LOHS for approximately 50 participants per allocated group. 100 participants allocated 1:1 to NA and chest drain groups, and assuming a true between-group difference of −2 days (in favour of NA) and SD of 4.6 days, provides 90% power to declare non-inferiority at the one-sided 2.5% significance level, using a non-inferiority margin of +1 day. If non-inferiority is declared, superiority will be assessed: this sample size will allow detection of a between-group difference in LOHS of 3 days with 90% power, or 2.6 days with 80% power, at the two-sided 5% significance level. With this sample size, the probability of declaring superiority (Bayesian assurance), assuming a prior informed by the synthesised mean between-group difference of −2.5 days, is 75%.

### Patient approach, recruitment and randomisation

Potentially eligible participants will be identified by clinical and research teams in the emergency, acute medical and respiratory departments. All potential participants will be given a patient information sheet (PIS) describing the study. The timing at which patients receive the PIS will vary, depending on their capacity at time of identification. Patients will require a chest X-ray to confirm presence of pneumothorax.

Following a confirmed diagnosis of SSP and eligibility assessment by the usual care team, eligible patients undergo a capacity assessment from a suitably trained clinical staff member. If at this point, the patient has capacity, they are approached in the ED/AMU for their consent to take part in the study.

When patients are judged to be unable to provide informed consent for themselves at the time a decision or action needs to be taken, they can be automatically enrolled in the trial under deferred consent. The patient will then receive the randomly allocated trial intervention. If patients regain capacity within 72 hours postrandomisation, they are approached and asked to provide consent to continue in the trial. If patients do not regain capacity within 72 hours of randomisation, a member of the research team seeks advice from a personal consultee or, if unavailable, a nominated consultee.

Participants are randomised immediately after SSP has been diagnosed and informed consent is provided or waiver of consent is applied. Participants are allocated in a 1:1 ratio to either NA (intervention group) or intercostal drain (comparator group) using a secure, internet-based system, RedCap Academic, designed and maintained by Exeter CTU. Randomisation uses a minimisation algorithm with a random element, with two minimisation factors: (1) first/recurrent pneumothorax and (2) underlying lung disease (COPD vs other).

### Trial interventions

In the intervention (NA) group, the treating physician will use a small-bore catheter connected to a three-way valve, a 60 mL syringe and a drainage bag. The procedure will be terminated when no more air can be aspirated, or if the amount of aspirated air exceeds approximately 2.5 L. Shortly after, a chest X-ray will be performed to assess the change in pneumothorax size. Decisions regarding further intervention should be guided by the degree of the participant’s symptoms and physiology. If the participant remains symptomatic (reporting ongoing significant breathlessness) or physiologically unstable and pneumothorax is ≥2 cm (chest wall to lung edge) then the chest X-ray should be used to determine if an ICD is feasible and to guide insertion site. If drain insertion is feasible, a small-bore ICD (≤14F) should be inserted with the Seldinger technique and attached to an underwater seal bottle. This will count as a subsequent pleural procedure.

In the comparator (usual care) group, the treating physician will use a small-bore ICD (≤14F) with the Seldinger technique. The ICD should be connected to a drainage system (the underwater seal bottle). A chest X-ray will be repeated following cessation of bubbling in the water seal in the chest drainage system. Once the chest X-ray demonstrates full lung re-expansion and cessation of bubbling in the water seal, the chest drain can be removed.

### Data collection

Due to the emergency setting of the trial, the minimum essential data will be collected prior to randomisation, which will allow randomisation to be performed quickly and prevent delay in patient treatment. Clinical data will be collected at baseline and at day 30 by participating site team members onto case report forms and participant-completed questionnaires. These are entered into a REDCap^25^ database for data cleaning and analysis. Access to the database is via a secure password-protected web interface. It is acknowledged that it may not be feasible, or appropriate, to complete participant-reported outcome measures (PROMs) straight away (eg, the participant is too symptomatic or does not have capacity prior to treatment starting for their SSP). The first PROMs will be collected as soon as feasible following randomisation (within 24 hours of randomisation) and after treatment delivery, to ensure that urgent treatment is not delayed. Participants will be asked to complete the paper questionnaire according to how they feel at the time of completion, rather than retrospectively. The questionnaire may be completed with the assistance of a researcher/member of the clinical team (or person with caring responsibility, for example, family member, if/where feasible). If the participant does not have capacity, then a consultee can be asked to complete the resource use questions but no other questionnaires. PROMs will then be collected daily for the first 5 days after randomisation and at day 30.

### Statistical analysis

Data obtained will be analysed according to the intention to treat principle and reported according to the CONSORT (Consolidated Standards of Reporting Trials) guidelines.^26^ The primary analysis will compare initial LOHS, up to day 30, between allocated groups using linear mixed effects modelling, adjusting for minimisation factors and other prespecified prognostic factors, and including site as a random effect, with bootstrapping considered as necessary to handle skewed data. Participants who have died during the trial will be excluded from the primary analysis but included in all further analysis of the primary outcome data. To ensure that this is a reasonable approach, a worst/best and best/worst imputation of the missing initial LOHS data due to death will be undertaken (where best and worst are defined as ±2 SD from the mean).^27^ The between-group mean difference in initial LOHS will be presented alongside the adjusted two-sided 95% CI. If the upper limit of the one-sided 97.5% CI lies below 1 day, non-inferiority will be declared and then superiority will be assessed against the null hypothesis of no between-group difference. All secondary analyses of the primary outcome will be under the non-inferiority framework in the first instance, and subsequently for superiority if non-inferiority is demonstrated. Secondary outcomes will be assessed only for superiority.

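### The primary analysis drops every participant who dies during the 30-day trial, including those already discharged alive whose initial stay is fully observed

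*Protocol article*

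**What the plan says.** The Statistical analysis section of the protocol article opens with the principle: "Data obtained will be analysed according to the intention to treat principle". It then sets the rule for deaths: "Participants who have died during the trial will be excluded from the primary analysis". The same sentence brings them back into every other analysis of the primary outcome. As a check on that rule, "a worst/best and best/worst imputation of the missing initial LOHS data due to death will be undertaken", with best and worst placed two standard deviations either side of the mean. Non-inferiority is declared when the upper 97.5% limit for the between-group difference is below 1 day. Secondary analyses of the primary outcome are also run under the non-inferiority framework first.

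The Primary outcome section defines the endpoint as "Initial LOHS from randomisation, up to 30 days after randomisation". The abstract gives the time window: "Participants are followed up for 30 days". The Sample size section goes from 110 recruited to about 50 per group with a recorded stay, "allowing for up to 5% mortality rate within 30 days and nominal loss to follow-up/incomplete routine LOHS data".

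**The concern.** The endpoint is complete once the initial admission ends. A participant discharged on day 4 who dies on day 20 has a known stay of 4 days, and the later death makes nothing missing. As written, the rule still removes that participant, because it depends on death at any time in the trial and not on death before discharge.

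Death occurs after randomisation and is itself a secondary outcome. Removing those who die leaves a comparison of survivors, which randomisation no longer protects and which does not fit the intention-to-treat statement in the same paragraph. If one arm has more deaths, or if those who die have different stays in the two arms, the estimated difference moves. The margin is only 1 day, so a modest shift could affect the verdict.

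**Working it through.** **The plan's own figure.** Inputs from Sample size: 50 per group, true difference −2 days, SD 4.6, margin +1 day, one-sided 2.5%. The distance from truth to margin is 3 days. The standard error is 4.6 × √(2/50) = 0.92. Power = Φ(3/0.92 − 1.96) = Φ(1.30) = 90.3%, so the stated 90% reproduces. The sample size is not in question.

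**Expected deaths.** 5% of 110 is 5.5, so 5 or 6. I use 6, with 55 per arm.

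**Shift caused by the exclusion.** Let the gap be the mean stay of those who die minus the mean stay of survivors. An arm's mean over all randomised equals the survivors' mean plus (deaths/55) × gap. If the gap is the same in both arms, leaving deaths out shifts the difference by

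(deaths in NA − deaths in ICD)/55 × gap.

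The article gives neither deaths by arm nor the stays of those who die. The gaps below are therefore assumptions: 2 days, one SD (4.6) and two SDs (9.2).

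| Deaths NA v ICD | Gap 2 | Gap 4.6 | Gap 9.2 |
|---|---|---|---|
| 3 v 3 | 0 | 0 | 0 |
| 4 v 2 | 0.07 | 0.17 | 0.33 |
| 5 v 1 | 0.15 | 0.33 | 0.67 |
| 6 v 0 | 0.22 | 0.50 | 1.00 |

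For example, 4 v 2 with a gap of 9.2 gives 2/55 × 9.2 = 0.33 day. With positive gaps, the arm with more deaths looks better under the exclusion. With negative gaps (early deaths, short stays) the sign reverses. Equal deaths do not guarantee a zero shift if the gaps differ: 3 v 3 with gaps of 9.2 and 2 gives 3/55 × (9.2 − 2) = 0.39 day.

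The table covers all deaths. The article does not say how many would follow discharge, so only part of each shift comes from discarding observed stays.

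**Type I error.** This was simulated with 55 per arm, normal data, SD 4.6, the true all-randomised difference set at +1 day, and 40,000 runs.

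| Mortality NA v ICD | Gap 4.6 | Gap 9.2 | Gap −4.6 |
|---|---|---|---|
| 5% v 5% | 2.4% | 2.5% | 2.5% |
| 8% v 2% | 4.8% | 8.7% | 1.1% |
| 10% v 0% | 7.4% | 17.4% | 0.6% |

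Keeping everyone holds the error at about 2.5% throughout. The unequal mortality rates are illustrations; nothing in the article predicts them.

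**The planned imputation.** With SD 4.6, two SDs is 9.2 days. With 3 deaths per arm, scoring one arm high and the other low moves the difference by 3/55 × 9.2 + 3/55 × 9.2 = 1.0 day, the whole margin, although deaths are balanced. The low value is negative whenever the mean is below 9.2 days. Using the medians cited in the Introduction as stand-ins for means, 5.5 − 9.2 = −3.7 and 2.5 − 9.2 = −6.7 days. With the 10-day average stay also cited there, it is 10 − 9.2 = 0.8, so a negative value is possible but not certain.

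**The case against.** The strongest reply is that the plan already deals with deaths. The sentence that excludes them also brings them into all further analyses of the primary outcome, and a deliberately severe imputation tests whether the exclusion was reasonable. The imputation refers to stays missing because of death, which suggests that the authors meant deaths before discharge. The loss is budgeted openly in the sample size, and the article condenses a fuller document. Much of this stands: a fragile result would probably be exposed. But the exclusion itself is fixed in the article without the limit that the imputation implies. The article also attaches no consequence for the verdict if the other analyses disagree with the primary one.

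A reader might also infer a larger effect. Scoring each death at the 30-day cap, with a mean stay of 5 days, gives (30 − 5)/55 = 0.45 day per net excess death and about 1.4 days for three. That measures one particular scoring rule, with every death in hospital and set to 30 days. It is not the effect of leaving deaths out, and it does not apply to someone discharged early who dies later. With 5 deaths and equal mortality, an imbalance of three or more has probability 12/32 = 37.5%. That figure counts both directions (18.75% with more deaths under NA) and describes chance imbalance without a mortality effect, where the simulated type I error stays at about 2.5%. Nor do the documents show that those who die have the longest stays, so no direction of bias can be asserted.

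**Conclusion.** The point holds as an error in the scope of the rule. Taken literally, the primary analysis deletes fully observed primary outcomes because of a later death, against its own intention-to-treat statement. Bias is possible in either direction and is conditional on mortality, or the stays of those who die, differing between arms. For 6 deaths in 110 and an equal gap of 2 to 9.2 days in both arms, the shift runs from 0 (3 v 3) through 0.07 to 0.33 day (4 v 2). It reaches 1.0 day only for 6 v 0 with the largest gap, against a +1 day margin. The gaps and splits are assumptions.

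The documents do not support the stronger conclusions that the exclusion favours NA, that the non-inferiority verdict is invalid, or that in-hospital deaths must be scored at 30 days and pass a compulsory second test. That last step would change the estimand at a high price. Mixing 95% at mean 5, SD 4.6 with 5% at 30 gives a mean of 6.25 and an SD of 7.06. At 55 per arm, power is then Φ(3/(7.06 × √(2/55)) − 1.96) = Φ(0.27), about 61%.

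**What to change.** Amend the exclusion sentence under Statistical analysis, and align the SAP with it, as follows:

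- Every randomised participant discharged alive from the initial admission keeps the observed initial stay in the primary analysis, even if they die later by day 30.
- The exclusion and the best/worst imputation apply only to deaths before initial discharge.
- For those in-hospital deaths, prespecify a supportive analysis reported beside the primary result. For example, use observed days to death, and the 30-day cap as an unfavourable value, in place of a possibly negative mean minus two SDs. Do not make it a mandatory second hurdle.

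The cost is wording only. Discharge times are already collected, and the restored participants add to the analysed number. Power would rise from 90.3% at 50 per arm towards a ceiling of 92.8% if all 55 per arm were kept (standard error 4.6 × √(2/55) = 0.877; Φ(3/0.877 − 1.96) = Φ(1.46)). The handling of in-hospital deaths remains a choice of estimand, which the supportive analysis makes visible without spending power.
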